### Measures

#### Primary and secondary outcome variables

Participant self-report data is collected via telephone interviews. The primary dependent variable—child SHSe—will be measured in two ways. First, child cotinine will be collected in urine samples taken at baseline and the 12-month follow-up. Second, child SHSe will be measured by parental report of the number of cigarettes to which the child is exposed each day during the 7 days prior to all assessment periods
[28]. The secondary dependent variable—parent’s smoking cessation—will be assessed via parent-reported 7-day point prevalence abstinence for the 7 days prior to assessment at 3- and 12-month follow-up. The 12-month parent cessation report will be cotinine-verified.

#### Covariates, mediators, and moderators

Three variables will be measured as potential covariates and possible moderators of intervention effects: nicotine dependence will be measured with the Fagerström Test for Nicotine Dependence
[29], symptoms of depression will be measured with the Center for Epidemiological Studies 10-item depression scale
[30], and a single self-report item will assess number of individuals who smoke daily in the home
[31]. Additional background factors, including demographics and smoking history variables will be assessed for possible association with outcomes. Three variables will be measured as potential intervention mediators: program support for smoking cessation will be measured with the short form of the Partner/Significant Other Interaction Questionnaire
[32] (adapted to focus on KiSS program support), coping skills will be measured with the Urge Management Coping Skills measure developed by the authors based on urge management coping strategies identified by O’Connell et al.
[33], and DiClemente’s Self-Efficacy measure
[34] will be used to measure people’s confidence in their ability to refrain from smoking in different situations.

#### Process measures and treatment fidelity

Intervention processes will be assessed in both conditions at multiple time points, with multiple methods, and at each level of intervention: AAR and BC. Process data will include counselors’ observations (e.g., number of sessions, participant engagement ratings) and participants’ reports (e.g., receipt of pediatrician advice and informational brochures). AAR treatment fidelity will be assessed at the clinic level and BC fidelity at the individual counselor level.

### Analytic plan

Child outcomes are continuous and the parent outcome is dichotomous. The predictor is intervention group (AAR + BC vs. AAR + AC). Additional covariates may include number of smokers in home, level of nicotine dependence, depressive symptoms, demographic, and smoking history. ANCOVA will be used for continuous outcomes and logistic regression will be used for the dichotomous outcome. Intention-to-treat analyses will be performed using multiple imputations with careful attention to missing data mechanisms. Potential covariates and effect modifiers will be considered as warranted. The influence of mediator variables, such as urge management coping skills, will be assessed using bootstrapping techniques that provide estimates of the indirect effects and test for their significance via confidence intervals
[35]. The SPSS macro developed by Preacher and Hayes to test multiple mediation models will be used to carry out the mediation analysis
[36].

Evidence for hypothesis 1 (child SHSe) will be provided by a significant negative coefficient for the indicator of AAR + BC participation. Evidence for hypothesis 2 (parent quit) will be provided by a significant positive coefficient for the indicator of AAR + BC participation. Evidence for hypothesis 3 (mediators) will be provided by significant associations between AAR + BC participation and social cognitive variables (positive) and between social cognitive variables and child SHSe (negative) and parent smoking (positive) outcomes. Evidence for hypothesis 4 (moderators) is exploratory; evidence for effect modification will be provided by significant coefficients associated with multiplicative composites between AAR + BC participation and potential moderating variables.

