### Aims and hypotheses

Aim 1: Test the primary hypothesis that an intervention integrating pediatric clinic-level quality improvement with individual-level behavioral counseling (AAR + BC) will be more effective in reducing children’s SHSe than a clinic-level quality improvement plus attention control intervention (AAR + AC). *Hypothesis:* Compared with children in the AAR + AC condition, those in the AAR + BC condition will have significantly greater reductions in SHSe from baseline to 3- and 12-month follow-up.

Aim 2: Test the secondary hypothesis that AAR + BC will be more effective in increasing parental quit rates than AAR + AC. *Hypothesis:* Compared with parents in the AAR + AC condition, parents in the AAR + BC condition will have a significantly greater smoking abstinence at 3- and 12-month follow-up.

Aim 3: Test hypotheses that social cognitive variables (social support, urge management coping skills, self-efficacy) will mediate effects of the AAR + BC intervention on outcomes. *Hypothesis*: Compared with parents in the AAR + AC condition, parents in the AAR + BC condition will report greater social support, coping skills, and self-efficacy related to smoking cessation and SHSe reduction from baseline to 3- and 12-month follow-up. In turn, these changes will account for between-group differences in child SHSe and parent cessation outcomes.

Aim 4: Explore factors that may affect outcomes and moderate intervention effects, including presence of other smokers at home, level of nicotine dependence, and depressive symptoms.

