### Procedures

Pediatric healthcare providers in partnering clinics will be trained to provide brief advice about child SHSe and to refer assenting parents to the KiSS research staff. The sampling frame includes any parent who meets the eligibility requirements following receipt of the clinic intervention and referral. Trained research assistants consent eligible participants and collect self-report data at baseline, 3-month end-of-treatment, and 12-month follow-up via structured telephone interviews. Interviewers are blind to participants’ intervention condition. Various procedures are used to reduce attrition, including reminder postcards and text messages, flexible scheduling, and financial retention incentives for completing different phases of the study.

Randomization is stratified by site and race using randomized permuted blocks of varying lengths. Because site and strata were not fixed design characteristics, the maximum number of allocations was generated within each combination of site and stratum. The project biostatistician provided the allocations to the data collection team in opaque sealed security envelopes. Randomization was seeded using values obtained from random.org. Participants are randomized prior to an orientation home visit that follows the baseline interview. Once a home visit appointment is confirmed, a research assistant takes the top envelope from the allocation pile to bring to the home visit. The envelope is opened immediately prior to the home visit to reveal the condition.

During the home visit, participants receive a binder with materials that are relevant to their assigned intervention condition and they provide a sample of the child’s urine for baseline cotinine assessment. The child’s urine is collected again at the 12-month follow-up. Parents who report quitting smoking at 12-month follow-up are asked to provide a biospecimen for cotinine verification of quit status.

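### Randomisation is stratified by site and race, but the stated analysis does not list site, leaves race optional and does not name the baseline outcome

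*Protocol article*

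**What the plan says.** On randomisation, the Procedures section states: "Randomization is stratified by site and race using randomized permuted blocks of varying lengths".

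On the models, the Analytic plan states: "The predictor is intervention group (AAR + BC vs. AAR + AC", closing that bracket. It then says "Additional covariates may include number of smokers in home, level of nicotine dependence, depressive symptoms, demographic, and smoking history", and "ANCOVA will be used for continuous outcomes and logistic regression will be used for the dichotomous outcome". Later it adds: "Potential covariates and effect modifiers will be considered as warranted". Evidence for hypotheses 1 and 2 is defined there as a significant coefficient for the arm indicator.

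On the baseline outcome, hypothesis 1 under Aims and hypotheses is that "those in the AAR + BC condition will have significantly greater reductions in SHSe from baseline to 3- and 12-month follow-up". Under Primary and secondary outcome variables, "child cotinine will be collected in urine samples taken at baseline and the 12-month follow-up".

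Under Covariates, mediators, and moderators, three variables (nicotine dependence, depressive symptoms, daily smokers in the home) are named as potential covariates. The text adds: "Additional background factors, including demographics and smoking history variables will be assessed for possible association with outcomes".

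**The concern.** Stratified permuted blocks make the arms more alike on site and race than simple randomisation would. The treatment estimate is therefore less variable than an unadjusted model assumes. A linear model that leaves the strata out puts their variance into the residual and reports a standard error that is too large. The precision bought at randomisation is not used in the test.

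The article is not silent on covariates. It gives a list, and that list omits one randomisation factor and makes the other optional, with inclusion left to judgement. Hypotheses 1 and 2 rest on the significance of the arm coefficient from this model, so its terms should be fixed. The baseline outcome, likely to be the most useful covariate, has to be inferred.

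**Working it through.** The article gives no figure on this point to reproduce: neither the share of outcome variance explained by site and race (R²) nor the correlation of baseline with follow-up (ρ). Both are assumed below.

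**Inputs from the Power analysis section**
- α = .025. Sidedness is not stated; two-sided is taken, so z = 2.2414.
- Effect size: d = .30, the top of the stated range of .20 to .30.
- 166 per arm with 25% to 30% attrition: 166 × .70 = 116 to 166 × .75 = 124 completers per arm. The figure used is 120.

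**Strata omitted, no baseline term**
- Reported SE divided by true SE = 1/√(1 − R²)
- True type I error = 2[1 − Φ(2.2414/√(1 − R²))]
- Power, strata omitted = Φ(.30/[√(1 − R²)·√(2/120)] − 2.2414/√(1 − R²))
- Power, strata included = Φ(.30/[√(1 − R²)·√(2/120)] − 2.2414)

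| Assumed R² | SE ratio | True error (nominal .025) | Power, strata omitted | Power, strata included |
|---|---|---|---|---|
| .05 | 1.026 | .0215 | .534 | .557 |
| .10 | 1.054 | .0181 | .535 | .582 |
| .20 | 1.118 | .0122 | .537 | .639 |

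These powers illustrate the loss only; whether 166 per arm is enough is a separate question.

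**Strata omitted, baseline outcome in the ANCOVA**

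Take ρ = .5 and suppose the strata shift baseline and follow-up by the same amount. The residual variance is 1 − ρ² = .75. The stratum part still in it is R²(1 − ρ)², that is .0125, .025 and .05 for the three values of R². The SE ratio becomes:
- R² = .05: √(.75/.7375) = 1.008
- R² = .10: √(.75/.725) = 1.017
- R² = .20: √(.75/.70) = 1.035

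**Simulation check** (240 completers, 8 strata assumed, permuted blocks of 2, 4 and 6, 4,000 runs, R² = .10, ρ = .5)
- Unadjusted: mean SE .1289 against an empirical SD of .1222, a ratio of 1.055; rejection rate under the null .020.
- Strata only: .1223 against .1221; rejection .026.
- Baseline only: .1118 against .1107, a ratio of 1.010; rejection .0238.
- At d = .30, baseline only gives power .67; baseline plus strata gives .69.

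The Monte Carlo standard error of a rejection rate near .025 is √(.025 × .975/4000) = .0025, so the simulation agrees with the formulas.

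These figures apply to the linear model. In the logistic quit model, omitting the strata mainly changes the estimand from a conditional to a marginal odds ratio. That was not simulated.

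**The case against.** The best defence is that this is a condensed article. Exact model terms usually belong in an analysis plan that is not shown, the list is permissive and excludes nothing, and demographics can cover race. ANCOVA with a hypothesis on reduction from baseline implies the baseline value as covariate, and with that term present the strata add little. Much of this stands. The missing baseline term is an unnamed term, not a contradiction, and the larger figures above apply only without it. What does not stand is that nothing is left: the list as written omits site and makes race optional.

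Two stronger readings are tempting, and the article does not support either.

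- **Covariates are selected by their observed association with the outcome, which inflates type I error.** The sentence on background factors sits under Measures. It states no inclusion rule for the primary model and fits the exploratory fourth aim at least as well. In a simulation with five optional covariates (assumed; 2,000 runs, Monte Carlo standard error about .0035), keeping covariates by outcome association left the error at .025 to .030, against .026 to .029 unadjusted. It rose, to .054 to .088, only when the set was chosen after seeing the treatment p-value, and no section says that will be done.
- **The standard errors are wrong in a way that threatens a positive result.** In the linear model the error runs the other way: a significant result would be significant despite it.

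Nor does anything in the article require nicotine dependence in the quit model.

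**Conclusion.** The point holds as a loss of efficiency and a gap in specification, not as a threat to validity. Site is absent from the stated analysis, race is at most optional, the covariate set is discretionary and the baseline outcome is implied but unnamed.

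For the continuous outcomes, leaving out the strata overstates the standard error by about 3% to 12% if no baseline term is fitted, and by about 1% to 3.5% if one is. This rests on an assumed R² of .05 to .20, on ρ = .5 for the second range, and on strata that act alike on baseline and follow-up. If site and race explain little of the outcome, the effect is negligible. It is worth correcting because the correction costs almost nothing.

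**What to change.** In the Analytic plan, or in the statistical analysis plan if that is where it is fixed:

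- State the primary child exposure model as 12-month outcome on arm, baseline value of the same outcome, site and race. Enter site and race as main effects, to avoid sparse site-by-race cells.
- Include site and race in the logistic model for parental quitting, and say that the odds ratio is conditional on them.
- Include site and race in the multiple-imputation model.
- Make adjustment for any further covariates a sensitivity analysis, in place of the present discretionary wording.

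The cost is a change of wording and a few degrees of freedom. Site and race are already recorded for randomisation, and baseline exposure is already measured.

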### Power analysis

Sample size was determined for the primary outcome (child cotinine) assuming power ≥ .80, α = .025, and a modest effect size (Cohen’s d = .20 - .30)
[37]. Power estimates were derived from preliminary analysis of data from the FRESH trial
[38], which indicated d ≥ .23 for child cotinine. Attrition is estimated to range from 25% to 30%. Based on these assumptions, sample size for recruitment was set at 166 per intervention arm (332 total).

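### The 166 per arm cannot be reproduced from the power, α, effect sizes and attrition from which the protocol says it follows

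*Protocol article*

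**What the plan says.** The protocol article has one power statement, in the Power analysis section, for child cotinine. It sets the sample size "assuming power ≥ .80, α = .025, and a modest effect size (Cohen’s d = .20 - .30". It refers to preliminary data from an earlier trial, "which indicated d ≥ .23 for child cotinine", and adds "Attrition is estimated to range from 25% to 30" percent. From these assumptions it concludes that "sample size for recruitment was set at 166 per intervention arm (332 total".

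The section does not say whether α is one- or two-sided, which formula was used, or whether covariate adjustment was counted. Two other places matter. The Analytic plan says "ANCOVA will be used for continuous outcomes", and the section on primary and secondary outcome variables says "child cotinine will be collected in urine samples taken at baseline and the 12-month follow-up". A baseline value is therefore available for adjustment.

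**The concern.** The article lists its inputs and says that the sample size rests on them, so a reader should be able to recover 166 per arm. Standardised effects of .20 to .30 usually need several hundred per arm at this α, and attrition of a quarter or more raises the number further. A figure of 166 looks too small on its face.

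This is the only power figure given, and it concerns the primary outcome. A reader who trusts it would take a non-significant result as fairly strong evidence against an effect of .20 to .30. If real power at those effects is well below 80%, the result does not support that reading.

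**Working it through.** **Inputs.** All come from the Power analysis section: power .80; α = .025, tried both ways because sidedness is not stated; d = .20, .23 and .30; attrition 25% and 30%; 166 recruited per arm, 1:1.

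**Step 1: attempt to reproduce 166.** For two equal groups, n per arm = 2(z_α + z_β)²/d², rounded up and then divided by (1 − attrition).

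- Two-sided: z_α + z_β = 2.2414 + 0.8416 = 3.0830, so n = 19.01/d².
- One-sided: 1.9600 + 0.8416 = 2.8016, so n = 15.70/d².

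| d | Two-sided: analysed per arm | recruited at 25% / 30% | One-sided: analysed per arm | recruited at 25% / 30% |
|---|---|---|---|---|
| .20 | 476 | 635 / 680 | 393 | 524 / 562 |
| .23 | 360 | 480 / 515 | 297 | 396 / 425 |
| .30 | 212 | 283 / 303 | 175 | 234 / 250 |

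The smallest entry is 234 (d = .30, one-sided, 25% attrition), which is 41% above 166 (234/166 = 1.41). Inflating by the common mistake of multiplying by (1 + attrition) gives 175 × 1.25 = 219, still well above 166.

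**Step 2: power that 166 per arm delivers, unadjusted.** Completers are 166 × .70 = 116.2 and 166 × .75 = 124.5, taken as 116 and 124. Power is from the two-sample t-test (noncentral t).

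| d | Two-sided, 116 / 124 | One-sided, 116 / 124 | All 166 analysed, two- / one-sided |
|---|---|---|---|
| .20 | 23.4% / 25.0% | 32.9% / 34.8% | 33.5% / 44.3% |
| .23 | 30.9% / 33.0% | 41.5% / 43.8% | 43.9% / 55.1% |
| .30 | 51.2% / 54.3% | 62.4% / 65.3% | 68.5% / 77.8% |

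No cell reaches 80%, even with no attrition at all.

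**Step 3: detectable effect at 80% power, unadjusted.** With 124 and 116 per arm it is d = .394 and .407 (two-sided), or .357 and .369 (one-sided). Both ranges lie above .30.

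**Step 4: what ANCOVA would need.** If d is scaled by the unadjusted SD, adjusting for baseline multiplies the variance by (1 − ρ²), where ρ is the baseline to 12-month correlation. The ρ that gives 80% power is √[1 − n d²/(2(z_α + z_β)²)]. For example, at d = .23, n = 116, two-sided: √(1 − 116 × .0529/19.01) = √.677 = .823.

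| d | ρ needed, two-sided (124 to 116) | ρ needed, one-sided (124 to 116) |
|---|---|---|
| .30 | .64 to .67 | .54 to .58 |
| .23 | .81 to .82 | .76 to .78 |
| .20 | .86 to .87 | .83 to .84 |

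As a cross-check, ρ = .65 at d = .30, two-sided, gives 211.2 × (1 − .4225) = 122 analysed per arm, or 163 to 175 recruited, which brackets 166.

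**The case against.** The strongest defence is the planned ANCOVA. Cotinine is measured at baseline, and a correlation of about .54 to .67, depending on sidedness, would give 80% power at d = .30, the top of the stated range. Because this is a condensed article, the correlation and the sidedness may stand in the full protocol or the preliminary trial data. Their absence here is not an error. The Analytic plan also words its evidence criteria directionally, so a one-sided .025 cannot be excluded. All of this stands, and it rules out three stronger readings that a reader might infer.

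- **That 166 comes only from an effect of about d = .40.** Unadjusted and two-sided, d = .40 gives 119 analysed and 159 to 170 recruited, which does bracket 166. So do d = .36 one-sided (122 analysed, 163 to 175 recruited) and d = .30 with ρ of about .65. The document does not show which route was taken, so no cause of the discrepancy can be named.
- **That power is simply 31–33%.** That figure holds for a two-sided, unadjusted test at d = .23. One-sided it is 42–44%. With an assumed ρ of .7 (replacing d by d/√(1 − .49)), it is about 58–61% two-sided or 69–71% one-sided. For the same reason, the text does not establish that an effect of this size would more likely be missed than found.
- **That d = .23 is the value the trial was planned on.** The section gives a range, and reports .23 as a lower bound from earlier data.

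The defence does not carry the whole claim. The paragraph asserts at least 80% power for a range that starts at d = .20, and neither it nor any other section mentions a correlation of the size needed there. Multiple imputation does not help either, since all 166 per arm with complete data would still fall short unadjusted.

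**Conclusion.** The statement is wrong as written: 166 per arm does not follow from the listed power, α, effect range and attrition under either sidedness. Without adjustment, the whole stated range of effects is covered by power of 23–54% (two-sided) or 33–65% (one-sided), against the claimed 80% or more.

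These figures assume 116 to 124 completers per arm, a single two-group comparison of a continuous outcome, and d scaled by the unadjusted SD. Baseline adjustment could make the claim true at d = .30 under a moderate, unreported correlation. At d = .23 it would take about .76 to .82, and at d = .20 about .83 to .87. Whether the trial is underpowered at d = .30 therefore cannot be settled from the article. That the stated inputs do not yield the stated number can be.

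**What to change.** Restate the Power analysis paragraph so that its figures follow from one another. Give the sidedness of α, the expected completers per arm (116 to 124), any assumed baseline to 12-month correlation of cotinine with its source, and the power or detectable effect that results. If no adjustment was assumed, the detectable effect at 80% power is d of about .39–.41 two-sided or .36–.37 one-sided. Remove the claim of at least 80% power across d = .20–.30 unless a stated correlation supports it. If a correlation was used and simply not reported, stating it resolves the point for the effects that it covers.

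The cost is the rewording of one paragraph and probably a less favourable stated power. Recruitment and analysis need not change.

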## Discussion

Current approaches to pediatric SHSe reduction have limitations that weaken potential effectiveness when implemented at a single level. The KiSS intervention addresses these limitations through an integrated multilevel approach to addressing parental smoking. The end result of this project will be a novel, efficacious and translatable model for addressing the significant public health problem of child SHSe. Delivering the intervention in communities that have the highest prevalence of tobacco use and tobacco-related morbidity and mortality could produce the greatest public health benefits. Existing, publically-supported community-based providers of smoking cessation services, such as quitlines, and large urban pediatric clinics that serve high-risk populations could adopt this model by developing mutually advantageous partnerships: Clinics could provide referrals to established service providers who, in turn, could offer home-based behavioral counseling and systems navigation. Findings from the secondary mediator and moderator aims will inform science and theory in this field by identifying how and for whom the intervention works.

The significance of this multilevel approach could be realized through its influence on improved clinical practice by: a) improving tobacco intervention training and resources, b) simplifying and minimizing steps necessary for pediatric providers to adhere to tobacco intervention guidelines, and c) providing clinics with a parental smoking referral resource that helps parents get tobacco dependence treatment medications and addresses tobacco use and exposure in contexts where children’s SHSe is the greatest. If successful, this approach could inform science by providing evidence about the efficacy of integrating pediatrics and behavioral health approaches. While existing evidence-based practice approaches may be effective in upper-income communities with relatively low tobacco morbidity and mortality risk, the proposed outreach approach may be especially effective and worth implementing in clinics serving low-income and other high-risk populations that experience greater challenges associated with smoking behavior change.

